## Abstract

**Background:**

Intensive treadmill training (TT) has been documented to improve gait parameters and functional independence in Parkinson’s Disease (PD), but the optimal intervention protocol and the criteria for tailoring the intervention to patients’ performances are lacking. TT may be integrated with augmented virtual reality (AVR), however, evidence of the effectiveness of this combined treatment is still limited. Moreover, prognostic biomarkers of rehabilitation, potentially useful to customize the treatment, are currently missing. The primary aim of this study is to compare the effects on gait performances of TT + AVR versus TT alone in II-III stage PD patients with gait disturbance. Secondary aims are to assess the effects on balance, gait parameters and other motor and non-motor symptoms, and patient’s satisfaction and adherence to the treatment. As an exploratory aim, the study attempts to identify biomarkers of neuroplasticity detecting changes in Neurofilament Light Chain concentration T0-T1 and to identify prognostic biomarkers associated to blood-derived Extracellular Vesicles.

**Methods:**

Single-center, randomized controlled single-blind trial comparing TT + AVR vs. TT in II-III stage PD patients with gait disturbances. Assessment will be performed at baseline (T0), end of training (T1), 3 (T2) and 6 months (T3, phone interview) from T1. The primary outcome is difference in gait performance assessed with the Tinetti Performance-Oriented Mobility Assessment gait scale at T1. Secondary outcomes are differences in gait performance at T2, in balance and spatial–temporal gait parameters at T1 and T2, patients’ satisfaction and adherence. Changes in falls, functional mobility, functional autonomy, cognition, mood, and quality of life will be also assessed at different timepoints. The G*Power software was used to estimate a sample size of 20 subjects per group (power 0.95, *α* < 0.05), raised to 24 per group to compensate for potential drop-outs. Both interventions will be customized and progressive, based on the participant’s performance, according to a predefined protocol.

**Conclusion:**

This study will provide data on the possible superiority of AVR-associated TT over conventional TT in improving gait and other motor and non-motor symptoms in persons with PD and gait disturbances. Results of the exploratory analysis could add information in the field of biomarker research in PD rehabilitation.

## Introduction

1

Parkinson’s Disease (PD) is a complex neurodegenerative disorder that affects from 1 to 2% of people over 65 years of age (1), characterized by multiple motor and non-motor symptoms (2). Among motor disturbances, gait disturbance is the key symptom of the disease, which can affect step length, walking speed, trunk oscillations, and arms’ pendular movements; freezing and festination phenomena are possible. Gait disturbance is often accompanied by alterations in posture and balance, and can be associated with falls, with a decisive impact on the autonomy and quality of life (QoL) of the patient and caregiver (3). The control of motor symptoms related to PD is mainly carried out with pharmacological therapy; in recent years, deep brain stimulation has also acquired an important role in the advanced phases of the disease (4). However, these interventions have some limitations, especially in the presence of balance and gait disturbances, and the literature highlights the importance of integrating rehabilitation into the care of patients with PD (5–7). Intensive walking training in PD has evidence of effectiveness, in particular in stride speed and length, on activities of daily living (8, 9) and in reducing falls (10). Among the rehabilitation interventions for improving walking in PD, conventional treadmill training (TT) has resulted to be more effective compared to no-TT rehabilitation in improving gait speed and stride length with moderate and low-quality evidence, respectively (11), highlighting the need to confirm these results with higher evidence and to establish an optimal intervention protocol including treatment personalization (12).

Regarding non-motor symptoms, cognitive impairment may associate or even precede motor symptoms in PD and can worsen over time from mild cognitive impairment to full-blown dementia during the disease course. Drugs give limited benefits to this disorder, making it essential to explore the effects of non-pharmacological approaches (13). Targeted cognitive training presents some evidence of effectiveness in patients with initial impairment, but a recent review suggests that TT produces even greater cognitive effects (14). Virtual reality (VR) is used in the motor and cognitive training of patients with various neurological diseases, including PD. VR refers to a computer-generated three-dimensional digital environment that can be explored and interacted with by a person. Augmented reality or augmented virtual reality (AVR) is the union between VR and real life. The person who experiences it can interact with virtual content in the real world. Computer-generated content is superimposed on reality through visual stimuli such as objects and films, tactile and olfactory sensations, and sounds. AVR is proposed as an interactive approach, that aims to amplify the effects of motor training, both directly and indirectly, increasing the patient’s motivation and satisfaction, promoting greater adherence and participation to treatment, and training also cognitive aspects of fall risk (14). For these reasons, AVR is considered an emerging and promising therapeutic tool in neurorehabilitation (15). In this regard, positive results emerged from the clinical trial of Gulcan et al. (16) in which AVR-VR TT has been demonstrated to be effective in PD on most of spatial–temporal gait parameters compared to conventional physical therapy.

Moreover, results from recent reviews dedicated to comparing the benefit of VR rehabilitation, including TT, versus conventional one showed that VR appears to be promising in motor outcomes such as gait and mobility (17–19), obtaining the most replicated and convincing result on balance (18–21); less evidence has been reported on functional autonomy (19) and QoL (18).

The Motek C-Mill is a recently developed treadmill for assessing and training gait and balance. By integrating AVR, audible and visual cues, and force platform technology, C-Mill enables obstacle avoidance training, dual-tasking applications, realistic VR environments, and a variety of balance challenges to promote balance strategies and gait adaptation and prepare patients to regain walking in daily life, using a safe and controlled environment. The integration with a force platform allows the acquisition of the trajectory of the center of pressure, automatically adapting the complexity of the tasks based on patient performance in real-time and returning feedback to the patient and the therapist to monitor progress and performance. The device was developed to treat gait disorders of various origins; in particular, the C-Mill has been used to study obstacle avoidance difficulties in PD (22, 23), but its effectiveness in the rehabilitation of these patients needs to be confirmed. Focusing on the comparison between conventional TT versus TT+AVR treatment effect on PD motor symptoms, current results are in favor of the TT+AVR for the gain obtained in incident falls in the long period (6 months) and in gait adaptability, a key target for reducing fall risk (22). These data come from 2 studies conducted on older at risk of falling, including cases affected by PD and results have been obtained using a quantitative method of gait assessment, the GaitRite mat (23, 24), preliminary data offering promising results on a possible benefit of interventions that combine TT and AVR in PD (25).

The integration of VR on TT in PD rehabilitation is an extremely current topic in PD rehabilitation research. Both interventions separately showed positive results on gait parameters (23–26), in particular stride speed and length and also balance, however, larger studies with a randomized controlled design are necessary to define recommendations for the use of VR and TT, isolated and in combination, in PD rehabilitation, to be applied according also to the patient characteristics.

Indeed, since the effect of rehabilitation may be different across motor subtypes (27) and disease severity (8), treatment personalization holds promise in PD rehabilitation. However, a timely optimization of personalized rehabilitation treatment for PD patients is nowadays at least in part limited by the lack of measurable biomarkers indicative of neuroplasticity phenomena and predictive of the response to the rehabilitation treatment. In this regard, Neurofilament Light Chain (NfL) has been recognized as a non-specific marker indicative of axonal damage in different neurological diseases (28–30), whereas it is not fully understood whether and how its concentration changes after rehabilitation treatment. In late phase after stroke the adaptive synaptic plasticity is supposed to be the main mechanism of NfL release, suggesting that this biomarker could also be useful to track the positive effects following rehabilitation (29). Recent literature suggests that neuroplasticity phenomena can be investigated with other innovative approaches, spanning from quantification of single molecules with highly sensitive technologies to more complex biomarkers like miRNome profile and circulating Extracellular Vesicles (cEVs) characterization. The study of the cellular processes taking place in the central nervous system in patients with PD before, during, and after rehabilitation might provide useful tools to correlate the severity of the damage and the peculiarities of the patient with the effectiveness of treatment. cEVs are natural nanoparticles defined as membrane-bound nanovesicles, released by body cells under physiological and pathological conditions as vehicles for bioactive molecules useful for intercellular communication. It has recently been demonstrated that biological fluids are rich in such vesicles, in particular vesicles originating from all the organs of our body, including the central nervous system, circulate in the blood (31). cEVs may change in concentration, dimension and biochemical content as a consequence of pathological processes and possibly after rehabilitation. In patients with PD, vesicles appear to play a role in the transport of molecules involved in the pathogenetic mechanisms of the disease itself, such as for example in the transport of the alpha-synuclein protein at the cerebral and peripheral level (32). The presence of cEVs involved in the pathogenesis and evolution of the disease and carriers of potential diagnostic markers has been demonstrated in peripheral blood (33). However, the size, heterogeneity, and large number of molecules present within and on cEVs have limited their use for diagnostic purposes. Raman spectroscopy is proposed as a useful method for the rapid and exhaustive biochemical characterization of circulating exosomes without the use of staining and labeling procedures. It has already been demonstrated how the Raman signature of cEVs can be correlated with some clinical scales commonly used for PD patient profiling, suggesting their potential use for patient stratification (34).

In summary, the evidence of the potential superiority of TT + AVR versus TT to improve gait in PD is still preliminary, and few studies include both clinical and instrumental gait measures, as it is instead recommended (3); further, an optimal TT(+AVR) protocol, customized to patients’ performances has not been established; finally, potential biomarkers of neuroplasticity and prognostic biomarkers are still under study.

Taking into account these considerations, the primary objective of this study is to compare the effects on gait performances of an integrated rehabilitation intervention before and after intensive rehabilitation with TT endowed of AVR, versus TT alone in patients with PD in II-III Hoehn and Yahr stage (35) with gait disturbances. The secondary objectives are to assess the effects of the interventions on balance performances, kinematic gait parameters and other motor and non motor symptoms immediately after treatment and at a 3-months follow up, and to assess the patient’s satisfaction and adherence to the treatment. The exploratory objective is to investigate potential serum biomarkers of neuroplasticity and prognosis.

## Methods and analysis

2

Consensus meetings were held with movement disorders experts (Azienda Ospedaliero Universitaria Careggi, Parkinson Unit, Florence), guided by a Neurologist ([name]) with more than 20 years expertise in PD, rehabilitation experts (Department of experimental and clinical medicine, University of Florence, IRCCS Fondazione Don Carlo Gnocchi of Florence), and biologists of the Laboratory of Nanomedicine and Clinical Biophotonics (LABION, IRCCS Fondazione Don Carlo Gnocchi of Milan), guided by [name] with more than 10 years of expertise in biomarkers research, to develop an extensive and feasible assessment protocol with the following requirements: (1) to identify variables that can be easily and reliably collected in an inpatient rehabilitation setting, using internationally recommended and validated tools, adopting, when available, Italian versions, (2) to gain objective measures of clinical and functional variables through instrumental assessment (3) to monitor changes in biological markers potentially indicative of neuroplasticity or predictive of rehabilitation outcomes.

In more detail, the clinical assessment protocol has been developed in collaboration with the Parkinson Unit by Neurologists, Neuropsychologists, Physiatrists and Physiotherapists with long-lasting clinical and research expertise in neurological rehabilitation; the rehabilitation intervention has been developed in collaboration with the Parkinson Unit and will be carried out by Physiotherapists with at least 5 years of expertise in the rehabilitation of PD patients; all assessments will be performed by researchers with similar clinical experience and background in neurorehabilitation research, blind to treatment assignment.

### Study design

2.1

This is a single-center, no-profit, parallel arm randomized controlled single-blind trial with an active comparator where the experimental intervention is represented by an TT+AVR and the comparator by a conventional TT.

Randomization will be performed by an external Researcher (not involved in the study design or procedures): a list of 0–1 will be generated using Phyton. Allocation will be concealed. Medical staff will propose consecutively the study for all eligible patients referring to the Parkinson Unit and the IRCCS Don Gnocchi Florence, assigning, in case of enrollment, an identification number to the participant.

Outcome raters will be blinded to the treatment assignment, including clinicians assessing the eligibility of patients and the raters (Neurologist, Physiatrist, Psychologist, Physiotherapist, Laboratory staff). Blindness will be ensured by the modality and timing of assessments at T0, T1, and T2 that will be conducted at times other than treatment and by raters not involved in the training. Blinding will be removed if requested by the participant at the end of the study and in case of undesirable effects.

The promoter of the study is the Department of Clinical and Experimental Medicine, University of Florence, Italy; the study will be performed at “Struttura Organizzativa Dipartimentale (SOD) di Riabilitazione Generale-Istituto di Ricovero e Cura a Carattere Scientifico (IRCCS) Fondazione Don Carlo Gnocchi, Florence.”

Two collaborators for external services will take part in the study:

The Movement Analysis Laboratory at IRCCS Don Carlo Gnocchi Florence, dedicated to instrumental data analysis (postural sway and gait analysis).The Laboratory of Nanomedicine and Clinical Biophotonics (LABION) at IRCCS Fondazione Don Carlo Gnocchi, in Milan, dedicated to biological data analysis.

The study received Ethical Committee approval from the local Institutional Review Board (Comitato Etico Regione Toscana – Area Vasta Centro) on the 5th of July 2022 (Approval Number: 20915_spe).

The registration on ClinicalTrials.gov has been completed and the study has been reviewed obtaining the identification number “NCT05902065.”

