### Sample size estimation

2.2

The sample size was estimated based on the primary outcome of the study “the evaluation of the difference in gait assessed by the Tinetti Performance-Oriented Mobility Assessment gait (POMA-G) scale (36) between the TT+AVR and the TT group at T1.” Data for the estimation were obtained from a previous study aiming to evaluate the effects of non-conventional TT (partial weight-supported TT) on patients with PD (37) using the POMA-G scale. Mean values observed in the POMA-G score after 4 weeks of treatment were 10.7 ± 1.1 and 11.7 ± 0.5, for the conventional gait training and partial weight-supported TT group, respectively, leading to a high effect size *d* = 1.17. Based on those data and assuming a statistical power of 95% and an *α* = 0.05, the resulting sample was 20 subjects per arm. Dropouts are expected to be around 20%. To compensate for possible dropouts, the enrolment of a further 8 patients has been deemed appropriate, reaching an estimate of 24 subjects per group. Thus, 48 patients will be enrolled starting from the date of Ethical Committee approval, within July 2024. The sample size has been estimated using G*Power software (38).

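### Nothing stated protects the POMA-G comparison against a chance Hoehn and Yahr II/III imbalance: the ANOVA has time and group only, and the allocation list is not described beyond being 0-1

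*Protocol article*

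**What the plan says.** **Allocation.** Section 2.1 (Study design) has an external researcher prepare the sequence: "a list of 0–1 will be generated using Phyton". It adds "Allocation will be concealed". It mentions no block, stratum, minimisation or fixed total per arm, and it does not call the randomisation simple or unrestricted.

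**Size.** Section 2.2 plans 20 evaluable patients per arm and adds a dropout allowance, "reaching an estimate of 24 subjects per group", 48 in total.

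**Population.** Section 2.3 admits Hoehn and Yahr stages II and III, so stage is known for every patient before allocation. The Introduction, arguing for personalised treatment, says that "the effect of rehabilitation may be different across motor subtypes (27) and disease severity (8").

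**Analysis.** Section 2.7.2 compares the arms at baseline with significance tests. It then names a two-way repeated measures ANOVA for the primary and secondary outcomes, with assessment time as the within-subject factor and group as the between-subject factor. Stage is not a factor or covariate.

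**The concern.** Both arms receive treadmill rehabilitation. If response to rehabilitation depends on severity, as the article says it may, stage predicts change in POMA-G in both arms. A chance surplus of stage III patients in one arm would then move the group-by-time contrast for reasons unrelated to augmented virtual reality.

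There are two usual protections: balance stage at allocation, or include it in the model. The article states neither. The baseline tests in 2.7.2 can show an imbalance but do not correct the estimate for it. In a single-centre trial of 48 patients, a visible stage imbalance would leave readers unsure how much of an observed difference to attribute to the intervention, and the model as stated offers no prespecified answer.

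**Working it through.** **1. The plan's own sample size.** Section 2.2 gives "Mean values observed in the POMA-G score after 4 weeks of treatment were 10.7 ± 1.1 and 11.7 ± 0.5", "leading to a high effect size *d* = 1.17", and "assuming a statistical power of 95% and an *α* = 0.05".
- d = (11.7 − 10.7) / √((1.1² + 0.5²)/2) = 1.0 / √0.73 = 1.170.
- A two-sided two-sample t-test (noncentral t) reaches 95.0% power at 20 per arm, so the figure of 20 is reproduced. The article does not state sidedness; two-sided is the reading that fits.
- 20 × 1.2 = 24 per arm, 48 in total.

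**2. Arm sizes if the list were unrestricted.** This is an assumption, with the number in one arm ~ Binomial(48, 0.5).
- P(exactly 24/24) = 11.5%.
- P(20/28 or more unequal) = 31.2%; P(smaller arm below 20) = 19.3%; P(18/30 or more unequal) = 11.1%.
- The central 95% range is 17 to 31 per arm.

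**3. What unequal arms cost.** The noncentrality is d·√(n₁n₂/(n₁+n₂)), with d = 1.17.

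| Split | n₁n₂/(n₁+n₂) | Power, all evaluable | Power after 20% loss in each arm |
|---|---|---|---|
| 24/24 | 12.00 | 97.8% | 94.2% |
| 20/28 | 11.67 | 97.5% | 93.6% |
| 18/30 | 11.25 | 97.0% | 92.7% |

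Averaged over all splits, unrestricted allocation of 48 gives 97.5%, against 97.8% for a forced 24/24, a loss of about 0.3 points.

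**4. Stage imbalance.** The article does not give the stage III share, so 20%, 30% and 50% are assumed (10, 14 and 24 of 48 patients). The table shows the probability that the stage III share differs between arms by at least 20 percentage points, from 400,000 simulated allocations per row.

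| Assumed stage III share | Unrestricted list | 24/24 forced, no strata |
|---|---|---|
| 20% | 10.7% | 7.2% |
| 30% | 14.2% | 11.0% |
| 50% | 19.4% | 14.8% |

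A gap of at least 10 points has probability 44% to 47% under an unrestricted list. Forcing equal arms therefore removes only part of the risk; stratifying by stage is what bounds it at allocation.

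**5. Effect on the estimate (illustration).** Suppose the stages differ in POMA-G change by δ points. A 20-point gap shifts the unadjusted contrast by 0.20 × δ. For δ from 0.5 to 2 (assumed; the article gives no figure) the shift is 0.10 to 0.40 points, against a planned difference of 11.7 − 10.7 = 1.0.

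**The case against.** **The article is silent on restriction; it does not deny it.** A reader might infer from 2.1 that allocation is simple randomisation without blocking or stratification. The text does not support that. A list of zeros and ones can be built in blocks, fixed at 24 of each, or generated separately by stage, and a condensed article may leave such detail to the full protocol. This objection stands, and it makes the probabilities in steps 2 and 4 conditional.

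**Arm size is close to irrelevant.** A reader might also infer that arms below 20 would undermine the power calculation. They would not: 20 per arm is an equal-allocation result, the larger arm compensates, and even 18/30 loses about 1 point of power. This also stands.

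**The repeated measures model already uses baseline.** POMA-G is measured at T0, and the group-by-time term compares change, so a stable difference in level between stages largely drops out. This stands in part. It does not remove a difference between stages in change, which is the possibility the Introduction raises.

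**The Introduction says only that response may differ.** It does so to motivate personalised treatment and does not establish stage as a prognostic factor for POMA-G. That is fair, and the size of any shift remains an assumption. Nor would stratification or a stage term by itself estimate whether the benefit of augmented virtual reality differs by stage; that would need an interaction with group.

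**Chance imbalance is not bias.** With a valid concealed list the comparison is unbiased in expectation. This stands: the cost lies in precision and in how the single realised result can be read.

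**Conclusion.** The point holds for the analysis, and conditionally for allocation. Section 2.7.2 fixes a model with time and group only, in a population spanning two severity stages that the article itself says may respond differently. Nothing stated in 2.1 bounds a stage imbalance between arms. If the list is unrestricted, a gap of 20 percentage points or more in stage III share has a probability of about 11% to 19%, given an assumed share of 20% to 50%.

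The importance is modest. The effect is on precision and interpretability, not expected bias. The documents do not show that allocation is unblocked or unstratified, and unequal arm sizes would not materially reduce power. The point merits action because stage is already recorded and the remedy in the analysis costs almost nothing.

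**What to change.** **Section 2.7.2 (whatever the form of the list).** Prespecify Hoehn and Yahr stage (II vs III) as a term in the POMA-G analysis. Either add stage and stage-by-time to the repeated measures ANOVA, or model POMA-G at T1 on group with baseline POMA-G and stage as covariates. Stage costs about one between-subject degree of freedom (46 to 45 with 48 patients and two groups) and needs no new data. This remains useful if recruitment has closed, provided it is fixed before the allocation codes are linked to outcomes.

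**Section 2.1.** State in one sentence whether the list is restricted (blocks or a fixed 24/24) and whether it is stratified by stage.
- If it is neither and allocation is still open, generate the remaining sequence in permuted blocks of randomly varying size, stratified by stage and held by the external researcher. The cost is a few lines in the existing script. Blocking makes assignments slightly more predictable at a single site, which varying block sizes and external custody keep small.
- If allocation is complete, keep the list as it is and rely on the stage term.
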